## **8.1 THE CONTROL ARM – BEST CURRENT PRACTICE**

1. **Post-CRT restaging** – The post-CRT MRI must be **performed within 4-6 weeks (no later than 10 weeks)** from completion of CRT.
2. The radiologist will be notified that the patient has been randomised into the control arm. Radiologist completes the **CONTROL ARM POST-TREATMENT MRI Form**.
3. **Surgery** is planned according to the baseline MRI and should be performed 6-12 weeks after CRT completion. A prepared **SURGERY Form** should be enclosed in the patient notes so that the surgeon can complete the form immediately after surgery.
4. A routine surgical follow up appointment will occur 4-6 weeks after surgery, therefore the **SURGICAL MORBIDITY** and **PATHOLOGY REPORTING Forms** should be completed at 6 weeks. These forms may be completed retrospectively up to 12 weeks after surgery but only complications that occur within the first 6 weeks should be recorded on the **SURGICAL MORBIDITY Form**.
5. **Adjuvant Chemotherapy** - Please complete the **CHEMOTHERAPY and TOXICITY Forms** at the end of each cycle i.e. at the end of each 3-weekly cycle of CAPOX (or single agent capecitabine) or at the end of each 2-weekly cycle of FOLFOX (or single agent 5-FU).
6. **Oncological outcomes** – 12 months from the completion of CRT please complete the **ANNUAL FOLLOW-UP Form**, and further **SURGICAL MORBIDITY** and **TOXICITY Forms** to capture late surgical complications and residual toxicity respectively. To avoid the inevitable distress caused by the relative of a dead patient receiving questionnaires, please ensure this is completed in parallel with the follow-up for Patient Reported Outcome Measures (PROMs).
7. **PROMs** – 12 months from the completion of CRT, the recruiting trial site will need to invite the patient to complete a postal questionnaire (**QUALITY OF LIFE forms**) that includes 40 questions about symptoms and quality of life. The patient will have completed the questionnaires at entry into the study and will be expecting to receive the forms. A freepost envelope addressed to the recruiting trial site will also be provided. If the patient does not initially respond please contact them by phone – to

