### **8.2.2 PROCEDURE IF A LOCAL REGROWTH IS DETECTED**

Patients with evidence of clinical or radiological local regrowth or pelvic relapse must be treated at least as urgently as a primary rectal cancer by the surgical team. Refer to suspected regrowth pathway in Section 8.2.3 below. Complete a **SURVEILLANCE CRF**. If patient proceeds to surgery Follow-up and CRF completion should be carried out according to the Control arm (Section 10.1, Assessment Schedule Control Arm and Section 11.1, Post-Surgery Follow Up). The **SURGERY, SURGICAL MORBIDITY** and **PATHOLOGY REPORTING Forms** should be completed when the patient undergoes surgery. If the colorectal MDT decision is to offer adjuvant therapy then the **CHEMOTHERAPY** and **TOXICITY Forms** should also be completed during treatment. The timing of the oncological outcomes, assessment of late surgical complications and PROMs should be completed as per protocol.

If patient refuses surgery or is not fit for surgery then a **DISCONTINUATION OF TRIAL TREATMENT Form** should be completed and the patient followed-up unless they withdraw consent to further data collection.

The patient is still eligible for analysis on an intention to treat basis.

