7. A routine surgical follow up appointment will occur 4-6 weeks after surgery, therefore the **SURGICAL MORBIDITY** and **PATHOLOGY REPORTING Forms** will be completed at 6 weeks. The **SURGICAL MORBIDITY Form** may be completed retrospectively up to 12 weeks after surgery but only complications that occur within the first 6 weeks should be recorded.

8. **Adjuvant Chemotherapy** - The patient will receive 12 weeks (4 cycles of CAPOX or 6 cycles of FOLFOX). Please complete the **CHEMOTHERAPY** and **TOXICITY Forms** at the end of each cycle i.e. at the end of each 3-weekly cycle of CAPOX (or single agent capecitabine) or at the end of each 2-weekly cycle of FOLFOX (or single agent 5-FU).
9. Oncological outcomes – 12 months from the end of CRT please complete the ANNUAL FOLLOW-UP Form, and a further **SURGICAL MORBIDITY** and **TOXICITY Forms** to capture late surgical complications and residual toxicity respectively. To avoid the inevitable distress caused by the relative of a dead patient receiving questionnaires, please ensure this is completed in parallel with the follow-up for Patient Reported Outcome Measures (PROMs).
10. **PROMs** -12 months from the end of CRT, the recruiting trial site will need to invite the patient to complete a postal questionnaire (**QUALITY OF LIFE Form**) that includes 40 questions about symptoms and quality of life. The patient will have completed the questionnaire at entry into the study and will be expecting to receive the forms. A freepost envelope addressed to the recruiting trial site will also be provided. If the patient does not initially respond please contact them by phone – to confirm the questionnaires arrived and to re-send if necessary. If there is no response send a second questionnaire at 2 weeks later. If there is no response by 12 weeks (15 months from the end of CRT), we will accept that the patient preferred not to take part. If the patient has a disability that prohibits them from completing the forms by hand we recommend reading the questions out over the phone.
11. **Oncological outcomes** – 24 months and 36 months following the end of CRT please complete the **ANNUAL FOLLOW-UP Form**.
12. **PROMs** - 36 months (not at 24 months) following the end of CRT the patients will be asked to complete the same **QUALITY OF LIFE form**.

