## 10. ASSESSMENT SCHEDULES

Please refer to the assessment schedules below for details of assessments to be performed, timelines and the CRFs to complete (further details relating to CRF completion can be found at the front of the CRF pack).

- Radiological assessment will be performed as per [Appendix 6](#) with synoptic reporting according to the allocated **POST-TREATMENT MRI FORM**.
- Chemotherapy toxicity will be assessed at the end of each cycle during treatment and residual toxicity assessed at the 12-month follow-up visit.
- When surgery is performed, surgical morbidity will be recorded intra-operatively and both early (6 weeks) and late (up to 12 months) surgical complications will be recorded post-operatively.
- **The QUALITY OF LIFE Form** will be completed by all patients at registration. For patients that undergo surgery the QoL forms should be completed again at 1 and 3 years following the completion of CRT. For patients who defer surgery the QoL forms should be completed at 1, 3 and 5 years from the time of CRT completion.
- Adverse events should be recorded from the date of the post-CRT MRI scan until 30 days after the patient's last dose of chemotherapy received during the intervention phase of the trial. Residual toxicity will be assessed at 12 months. Concurrent medications should be recorded at registration and updated from randomization until 30 days after the patient's last dose of chemotherapy. .
- **ANNUAL FOLLOW-UP Forms** should be completed at 12 months from the end of CRT and annually thereafter up to 3 years in those that undergo surgery and up to 5 years in those who defer surgery.

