### 14.2.2 SECONDARY ENDPOINTS

All secondary endpoints will be summarised using descriptive statistics, and will be used to inform the design of the proposed phase III study. The following limited number of endpoints will be summarised by arm, and within arm by patients grouped by mrTRG 1-2 vs. 3-5. Exploratory comparison between arms will be carried out using Fisher's exact test for categorical variables (pCRM rate, proportion with unsalvageable regrowth, proportion of patients with any one or more grade 3-5 toxicity). Quality of surgery and surgical morbidity (maximum Clavien-Dindo grade per patient) will be compared between arms using a Mann-Whitney test. No other formal statistical comparison will be made between arms or mrTRG subgroups for endpoints not listed below.

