#### **Control arm versus Intervention arm: all patients**

- The pCRM rate will be compared between the control and investigation arms.
- The strength of agreement of the reported mrTRG will be tested for the site radiologist versus the central radiologist. An MRI training dataset will be used prior to site initiation and a kappa agreement of 0.7 or greater will be required for the site radiologist to be eligible to recruit to the study. The agreement between the recruiting radiologists and central radiologist scored mrTRG grades for scans acquired during the study for patients randomised to the intervention arm will also be assessed retrospectively at the end of the feasibility trial. The agreement between the recruiting radiologists and central radiologist scored mrTRG grades for scans acquired during the study for patients randomised to the intervention arm will also be assessed retrospectively at the end of the feasibility trial.
- Early (30 day) and late (up to 12 months) surgical morbidity will be reported according to the Clavien-Dindo classification
- Quality of surgery will be determined by using the mesorectal grading system and a similar system will be used for grading the quality of APE specimens (Pathology appendix). Outcomes will be compared between the control and intervention arms on an intention to treat basis.

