### SURGICAL MORBIDITY

All of the patients in this trial will have received radiotherapy and chemotherapy prior to surgery, which is believed to increase surgical morbidity. This is of greatest importance for those patients initially managed by deferral of surgery who later require surgery due to tumour regrowth.

Intra-operative and post-operative data will be collected. Post-operative complications will be recorded by clavien-dindo classification (table below). An anastomotic leak is defined as a clinically suspected leak, confirmed radiologically or at re-operation. Severity of anastomotic leakage should be graded according to the impact on clinical management: Grade A anastomotic leakage results in no change in patients management, whereas grade B leakage requires active therapeutic intervention but is manageable without re-laparotomy. Grade C anastomotic leakage requires re-laparotomy.

| Surgical Morbidity: Clavien-Dindo Classification |                                                                                                                                                                                                                                                                                              |
|----------------------------------------------------------------------|----------------------------------------------------------------------------------------------------------------------------------------------------------------------------------------------------------------------------------------------------------------------------------------------|
| Grade 1                                                       | Any deviation from the normal postoperative course without the need for pharmacological treatment or surgical, endoscopic and radiological interventions. Acceptable therapeutic regimens are: drugs as antiemetics, antipyretics, analgesics, diuretics and electrolytes and physiotherapy. |
| Grade 2                                                       | Requiring pharmacological treatment with drugs other than such allowed for grade I complications. Blood transfusions and total parenteral nutrition are also included.                                                                                                                       |

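### The late surgical morbidity form is timed from the end of chemoradiotherapy, not from surgery, so operated patients in the two arms are observed for unequal times

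*Protocol*

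**What the plan says.** Section 14.2.2 plans an exploratory comparison in which "surgical morbidity (maximum Clavien-Dindo grade per patient) will be compared between arms using a Mann-Whitney test". It does not say which period the maximum is taken over. The list that follows states: "Early (30 day) and late (up to 12 months) surgical morbidity will be reported according to the Clavien-Dindo classification". Section 4.4.2 has the same wording. Section 10 says that "both early (6 weeks) and late (up to 12 months) surgical complications will be recorded post-operatively". None of these gives the starting point of the 12 months.

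The working instructions do give one:

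- **Control arm, section 8.1 item 6:** "12 months from the completion of CRT please complete the" annual follow-up form, with a further surgical morbidity form, the latter "to capture late surgical complications and residual toxicity respectively".
- **Poor responders, section 8.3 item 9:** "12 months from the end of CRT please complete the ANNUAL FOLLOW-UP Form, and a further" surgical morbidity form.
- **Schedules 10.1 and 10.3:** the late surgical morbidity entry sits in the 12-month column, counted from the end of CRT.
- **Surgery for regrowth, section 8.2.2:** the surgery, morbidity and pathology forms are completed at the operation, but "assessment of late surgical complications and PROMs should be completed as per protocol". Section 10.2 refers these patients to the control schedule.

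On morbidity in patients operated on after radiotherapy and chemotherapy, Appendix 4 adds: "This is of greatest importance for those patients initially managed by deferral of surgery who later require surgery due to tumour regrowth".

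**The concern.** A late assessment at a fixed time after CRT is a fixed time after surgery only if surgery happens at the same time in both arms. Here the intervention moves it: poor responders have 12 weeks of extra chemotherapy first, and patients who defer may be operated on years later. A maximum grade can only stay the same or rise as observation lengthens, so the arm operated on later has less opportunity to show a high grade even if true morbidity is equal.

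At stake is a safety comparison meant to inform the phase III design. Section 3.1 also carries the feasibility patients into the final phase III analysis, so late data not requested now would be missing there too.

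**Working it through.** The protocol states no length of observation after surgery, so there is no figure of its own to reproduce. The check is calendar arithmetic in weeks from the end of CRT, with the late form at week 52.

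**Inputs**
- Control surgery: weeks 6-12 (section 8.1).
- Poor responders: 12 weeks of chemotherapy starting by week 12, then surgery 6-12 weeks after it ends (section 8.3).
- Earliest chemotherapy start: after the restaging MRI, which is planned at 4-6 weeks (Appendix 1, section 2). No earliest date is stated; week 4 is taken as an assumption, and it is the one that narrows the gap most.
- Early form: complications in the first 6 weeks after surgery (sections 8.1 and 8.3).

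**Time observed after surgery = 52 − week of surgery**

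| | Week of surgery | Weeks observed | Beyond the 6-week form |
|---|---|---|---|
| Control | 6 to 12 | 52−12 = 40 to 52−6 = 46 | 34 to 40 |
| Poor responders, operated | 4+12+6 = 22 to 12+12+12 = 36 | 52−36 = 16 to 52−22 = 30 | 10 to 24 |
| Surgery for regrowth after month 12 | after 52 | early form only | 0 |

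The first two ranges do not overlap. If chemotherapy starts at week 6, the upper limit for poor responders falls to 52−24 = 28. One 3-week toxicity delay lowers the lower limit to 52−39 = 13.

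**Late complications alone (illustration).** Assume the same constant hazard in both arms and a late risk r over 37 weeks, the midpoint of 34-40. Then h = −ln(1−r)/37, and the share seen in w weeks is 1 − exp(−hw).

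| r in control | w = 10 | w = 17 | w = 24 |
|---|---|---|---|
| 10% | 2.8% | 4.7% | 6.6% |
| 15% | 4.3% | 7.2% | 10.0% |
| 20% | 5.9% | 9.7% | 13.5% |

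**Any complication, early or late.** This is closer to what a maximum grade reflects. Take 15% against 7.2% late, an assumed early risk e equal in both arms, and independence. The share with any complication is 1 − (1−e)(1−late).

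| e | Control | Poor responders | Difference |
|---|---|---|---|
| 30% | 1 − 0.70×0.85 = 40.5% | 1 − 0.70×0.928 = 35.0% | 5.5 points |
| 40% | 1 − 0.60×0.85 = 49.0% | 1 − 0.60×0.928 = 44.3% | 4.7 points |
| 50% | 1 − 0.50×0.85 = 57.5% | 1 − 0.50×0.928 = 53.6% | 3.9 points |

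These risks are assumptions; the protocol gives none.

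**The case against.** The case for leaving the plan alone has several parts.

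- **The test may not use late data.** Section 14.2.2 does not name the window, and secondary objective 3 (section 4.2) concerns 30-day morbidity reported descriptively. Section 14.2.2 also leaves methods and timing to a statistical analysis plan. This stands: that the test pools unequal late windows is an inference. But an analysis plan can choose a window only among data collected, and cannot recover late complications that no form requests.
- **Early morbidity is seen equally.** The early form runs from the date of surgery in every operated patient. This stands, and it limits the effect. A reader might infer from the late-only table that apparent morbidity would be halved. The documents do not support that: the tested quantity is the maximum grade, which early complications also set, and the table rests on an assumed constant hazard. If late hazard falls with time since surgery, the gap shrinks.
- **Regrowth surgery is covered.** A reader might infer that operations after month 12 go unobserved altogether. Section 8.2.2 rules this out, because the morbidity form is completed at the operation. Only the late part is uncovered, and its timing there is left to the general rule.
- **Adverse event forms also record surgical events.** Appendix 1 requires this, but only until 30 days after the last chemotherapy dose, with CTCAE grading. With adjuvant treatment starting 4-12 weeks after surgery and lasting 24 weeks in control and 12 in poor responders, and 30 days taken as about 4 weeks, that window closes at about 4+24+4 = 32 to 12+24+4 = 40 weeks against 4+12+4 = 20 to 12+12+4 = 28. It is unequal too, so it softens the gap without closing it.
- **The comparison is exploratory** in a 90-patient trial whose primary endpoint is recruitment. This lowers the weight of the point but does not remove the direction of the bias.

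**Conclusion.** The point holds in a limited form. Late surgical morbidity has no stated time origin, and the form that collects it is tied to the end of CRT. Operated control patients are observed for 40-46 weeks after surgery and operated poor responders for about 16-30 weeks, taking week 4 as the earliest chemotherapy start. Surgery for regrowth after month 12 has no scheduled late assessment.

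If the Mann-Whitney test includes late complications, the unequal windows push it towards lower morbidity in the intervention arm. Under the assumptions shown, the shift in the share of operated patients with any complication is roughly 4 to 5.5 points, against about 8 points (15% − 7.2%) for late complications alone. The effect on the whole-arm comparison cannot be computed: it depends on how many intervention patients are operated on, when, and how those who defer surgery are counted. The point is worth correcting because late data not requested cannot be restored later. It does not threaten the primary endpoint.

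**What to change.** 1. Make the late surgical morbidity form due 12 months after the date of surgery in every operated patient, including surgery for regrowth (sections 8.1, 8.2.2, 8.3 and 10.1-10.3). Leave the annual follow-up form on the CRT clock.
2. State that origin in sections 4.4.2 and 14.2.2.
3. Limit the between-arm test to a window from surgery that is common to all operated patients. For the feasibility report, use the early window, naming either 30 days or 6 weeks since the protocol uses both. Report late morbidity descriptively, with time observed since surgery.

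**Cost.** The change is to one form's due date and a few lines of text; no treatment, visit or procedure changes. Sites complete the form on a separate date from the annual form. It would fall at weeks 6+52 = 58 to 12+52 = 64 after CRT in control and 22+52 = 74 to 36+52 = 88 in poor responders. Late data therefore arrive later. Because surveillance of deferred patients runs to year 5, an operation then would report in year 6, so late morbidity after regrowth surgery may be incomplete at the feasibility analysis. If the schedule is not changed, step 3 alone removes the bias from the test but does not recover the late data.

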#### **Control arm versus Intervention arm: all patients**

- The pCRM rate will be compared between the control and investigation arms.
- The strength of agreement of the reported mrTRG will be tested for the site radiologist versus the central radiologist. An MRI training dataset will be used prior to site initiation and a kappa agreement of 0.7 or greater will be required for the site radiologist to be eligible to recruit to the study. The agreement between the recruiting radiologists and central radiologist scored mrTRG grades for scans acquired during the study for patients randomised to the intervention arm will also be assessed retrospectively at the end of the feasibility trial. The agreement between the recruiting radiologists and central radiologist scored mrTRG grades for scans acquired during the study for patients randomised to the intervention arm will also be assessed retrospectively at the end of the feasibility trial.
- Early (30 day) and late (up to 12 months) surgical morbidity will be reported according to the Clavien-Dindo classification
- Quality of surgery will be determined by using the mesorectal grading system and a similar system will be used for grading the quality of APE specimens (Pathology appendix). Outcomes will be compared between the control and intervention arms on an intention to treat basis.

#### **Control arm versus Intervention arm: good responders (mrTRG1&2)**

- The pCRM involvement rate in the good responders of the control versus intervention arm
- The proportion of patients with unsalvageable regrowth (defined in section 11.3). Greater than 5% unsalvageable regrowth may lead to premature closure of the trial or decision not to proceed to the phase III study.

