## 8. SUMMARISED PATIENT PATHWAYS

[figure not shown]

a Scheduled to receive 45 Gy-55Gy long course radiotherapy (inclusion criterion 4). b Treatment decision should be made prior to registration (planned choice is a randomisation stratification variable). Medical oncologist may choose to use CAPOX or FOLFOX, or single agent capecitabine or 5-FU if concomitant use of oxaliplatin is contraindicated. c If patient defers surgery then the remaining 12 weeks of chemotherapy should be given as soon as possible following the repeat MRI scan and MDT meeting.

The trial design gives rise to three possible pathways: Control Arm; Intervention Arm Good Response to CRT and Intervention Arm Poor Response to CRT. Investigators should ensure the patient pathways described in this protocol are followed. However, if an individual patient deviates from the planned pathway through their choice, e.g. patient in the 'good response' subgroup of the Intervention arm opts for surgery, then this should be recorded on the **PROTOCOL DEVIATION Form**.

All patients should follow the registration and randomisation procedure described in Section 7 of the protocol. Following Randomisation the PI at each site will be informed of which arm the patient has been randomised to and the appropriate patient pathway described below should be followed:

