### **8.2.1 PROCEDURE IF A PATIENT DECLINES DEFERRAL OF SURGERY**

Complete a **PROTOCOL DEVIATION Form**. Follow-up and completion of CRFs should be carried out according to the control arm (Section 10.1, Assessment Schedule Control Arm and Section 11.1, Post-Surgery Follow Up). The patient is still eligible for analysis on an intention to treat basis.

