### 8.3 EXPERIMENTAL ARM – A ‘POOR RESPONSE’ TO CHEMORADIOOTHERAPY

1. **Post-CRT restaging** – The post-CRT MRI must be performed within 4-6 (no later than 10) weeks of completing CRT.
2. Radiologist completes the **INTERVENTION ARM POST-TREATMENT MRI Form – mrTRG 3 –5 reported.**
3. **mrTRG directed management results in the patient being offered additional chemotherapy before a decision is made regarding surgery.**
4. The option of **additional pre-operative chemotherapy** is discussed with the patient. **Chemotherapy** (Appendix 2) – The patient will receive 12 weeks (4 cycles of CAPOX or 6 cycles of FOLFOX); this should start within 12 weeks of CRT completion. Please complete the **CHEMOTHERAPY** and **TOXICITY Forms** at the end of each cycle i.e. at the end of each 3-weekly cycle of CAPOX (or single agent capecitabine) or at the end of each 2-weekly cycle of FOLFOX (or single agent 5-FU).
5. Following the completion of 12 weeks of chemotherapy a repeat MRI should be performed 4-6 weeks later and mrTRG reported. Ensure the Radiologist receives the appropriate reporting form – **INTERVENTION ARM POST-TREATMENT MRI Form** which includes the mrTRG data fields. The Radiologist completes the **INTERVENTION ARM POST-TREATMENT MRI Form**.

**mrTRG directed management results in the patient being offered deferral of surgery (if mrTRG improved to I or II) or proceeding to surgery (mrTRG remains III-V). The options of surgery or deferral of surgery as appropriate should be discussed with the patient.**

- If mrTRG now I or II and it is agreed that patient should defer surgery then patients should receive the remaining 12 weeks of chemotherapy as soon as possible following the repeat MRI and MDT meeting and be followed up in the same way as those in the ‘good-response’ sub-group described above and undergo the 5 year surveillance schedule detailed in Section 11.2.1.

- If mrTRG remains III-V then patient proceeds to surgery and undergoes the following:

6. **Surgery** is planned according to the baseline and post-treatment MRI and should be performed **6-12 weeks after pre-operative chemotherapy** is completed. A prepared **SURGERY Form** should be enclosed in the patient notes so that the surgeon can complete the form immediately after surgery.

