### 11.3 DEFINITIONS REQUIRED FOR FOLLOW-UP

**Complete response** is defined as undetectable disease at the site of the primary tumour following pre-operative chemotherapy and/or radiotherapy. A pre-fix to denote the mode of assessment must also be included - clinical (c), MRI (mr) and pathology (p).

**Disease recurrence** is defined as either evidence of loco-regional recurrence or established metastatic disease. The time to the event is measured from the start of chemoradiotherapy to the date of the diagnostic investigation or MDT.

**Regrowth** is defined as the first recorded evidence of disease at the site of the primary tumour, in a patient with previous investigations suggesting an apparent complete response or undetectable disease (mrTRG1&2). The terms 'early regrowth' and 'late regrowth' will not be used in the trial.

**Unsalvageable regrowth** is defined as a tumour with radiological evidence of a good response that is initially managed by deferral of surgery but progresses. The extent of progression means that pCRM involvement becomes inevitable and so surgery is not performed, or pCRM involvement occurs when surgery is attempted.

**Loco-regional recurrence** (one of):

- Clinical recurrence with biopsy proof of recurrence
- CEA elevation and enlarging or new mass (includes pelvic, nodal and peritoneal disease). Biopsy confirmation is contraindicated or not feasible
- CEA non-secretors: enlarging or new mass (includes pelvic, nodal and peritoneal disease). Biopsy confirmation is contraindicated or not feasible (with or without PET/CT confirmation)

**Distant Metastases** (one of):

- This is defined as any confirmed evidence of disease above the L5/S1 junction
- Clinical recurrence with biopsy proof of recurrence
- CEA elevation and evidence of distant metastases. Biopsy confirmation is contraindicated or not feasible

- CEA non-secretors: evidence of distant metastases. Biopsy confirmation is contraindicated or not feasible (with or without PET/CT confirmation). Initial report to Trials Unit should define this as SUSPECTED. A further report 6 months later should define this as CONFIRMED if supported by MDT review.

***Inoperable Disease*** (one of):

- MDT decision that the local extent of disease on the post CRT pelvic MRI is not resectable
- At laparotomy the local extent of disease is not resectable

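### The 5% unsalvageable-regrowth limit is set for good responders only, so poor responders who improve after chemotherapy and then defer surgery fall outside it

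*Protocol*

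**What the plan says.** Protocol section 14.2.2 has three endpoint lists: all patients, good responders and poor responders. The limit is in the second, headed "Control arm versus Intervention arm: good responders (mrTRG1&2"), and reads "The proportion of patients with unsalvageable regrowth (defined in section 11.3). Greater than 5% unsalvageable regrowth may lead to premature closure of the trial", or to a decision against going on to phase III. The poor-responder list contains only acute toxicity.

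Section 8 names three pathways: "Control Arm; Intervention Arm Good Response to CRT and Intervention Arm Poor Response to CRT". Sections 8.2 and 8.3 assign the two intervention pathways from the post-CRT MRI.

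Under section 8.3, item 5, a poor responder has 12 weeks of chemotherapy and a repeat MRI. This "results in the patient being offered deferral of surgery (if mrTRG improved to I or II"). Patients who then defer are followed like the good-response sub-group; neither section 8.3 nor the schedule in section 10.3 says that they join it.

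Section 11.3 defines unsalvageable regrowth as "a tumour with radiological evidence of a good response that is initially managed by deferral of surgery but progresses", to the point where margin involvement is inevitable or is found at surgery. The definition does not name the MRI at which the good response was seen. Section 4.2, objective 4, says that inoperable regrowth will be considered in patients managed by deferral, without separating routes and without a threshold.

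**The concern.** Deferral is the part of the strategy whose main hazard is a tumour that regrows beyond rescue, and the 5% figure is the only numeric limit the protocol attaches to that hazard. Such a limit should cover everyone exposed to deferral. As placed, it covers those who enter after the post-CRT MRI and omits those who enter after the post-chemotherapy MRI, whose tumours first responded poorly. A cluster of unsalvageable regrowths in the second group would leave the stated proportion unchanged. The figure meant to inform early closure, or the decision on phase III, would then describe only part of the deferral experience.

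**Working it through.** The 5% limit has no derivation in the protocol, so there is no calculation to reproduce. The check is of who is counted, and then of how many could be missed.

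**Step 1: who is counted.**
- Event (11.3): good response on imaging, initial deferral, then progression. Both entry routes qualify.
- Exposure (8.2 and 8.3): deferral after mrTRG 1-2 at the post-CRT MRI, or after improvement to I-II at the post-chemotherapy MRI.
- Limit (14.2.2): good responders, mrTRG1&2. With the pathway names in section 8, this is the first route only.
- Objective (4.2): patients managed by deferral, hence both routes, but with no limit.

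The event definition and the objective cover both routes; the limit covers one.

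**Step 2: how many deferring patients are outside the limit.**

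Inputs from the protocol: planned sample size 90 (Trial Summary) and 2:1 allocation (3.2), so 90 × 2/3 = 60 intervention patients. The nearest figure for the good-response share is the statement in section 1 that up to 30% have a complete or near complete response.

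Assumptions: good-response share s = 30-50%; share of poor responders who convert and defer c = 10-30%; every good responder defers.

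Share outside the limit = 60(1−s)c / [60s + 60(1−s)c]

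| s | c = 10% | c = 20% | c = 30% |
|---|---|---|---|
| 30% | 4.2/22.2 = 19% | 8.4/26.4 = 32% | 12.6/30.6 = 41% |
| 40% | 3.6/27.6 = 13% | 7.2/31.2 = 23% | 10.8/34.8 = 31% |
| 50% | 3/33 = 9% | 6/36 = 17% | 9/39 = 23% |

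The range is 9% to 41%. If some good responders decline deferral, the share rises. With s = 30%, c = 30% and 30% declining, 18 × 0.7 = 12.6 good responders defer, and the share is 12.6/(12.6 + 12.6) = 50%.

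**Step 3: what the gap can hide.** Take s = 40% and c = 20%: 24 good responders, all deferring, and 36 × 0.2 ≈ 7 converters. Suppose two converters have unsalvageable regrowth and no good responder does. The limit reads 0/24 = 0%. Among all who deferred the proportion is 2/31 = 6.5%, and in the converter route 2/7 = 29%.

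**Step 4: why a pooled figure alone is not enough.** Take s = 30%: 18 good responders, of whom 14 defer (about 20% declining, assumed), and 42 × 0.2 ≈ 8 converters. Suppose there is one event, in a good responder. Among all good responders it is 1/18 = 5.6%, among those who deferred by that route 1/14 = 7.1%, and among all who deferred 1/22 = 4.5%. Pooling alone would bring this event below 5%, so the routes must also be shown separately.

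**The case against.** The limit is advisory: it says that exceeding 5% may lead to closure. Converter events are not lost. Any unsalvageable regrowth goes on the ADVERSE EVENT and SURVEILLANCE Forms (section 11.2.1, footnote d; Appendix 1, section 2), and the DMEC receives safety analyses and any others it requests (13.4.2). The opening of 14.2.2 also provides summaries by arm and by mrTRG 1-2 versus 3-5, where converter events can appear. All of this stands, and it limits the seriousness of the point. It does not bring those events within the stated limit.

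It can also be said that 14.2.2 does not name the MRI that defines mrTRG1&2, so converters might have been meant. That is possible, but the pathway names and the wording on converters' follow-up favour exclusion. If inclusion was intended, the text needs to say so.

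A reader might go further and infer that good responders who decline deferral dilute the rate. Section 8.2.1 says of such a patient: "The patient is still eligible for analysis on an intention to treat basis". They cannot have an event that requires deferral. The protocol does not establish this dilution, however. The regrowth bullet states no denominator, and in the 14.2.2 lists the intention-to-treat wording is attached to quality of surgery and toxicity, not to this bullet. An analysis plan could settle the denominator, and an intention-to-treat proportion would be a legitimate measure of the strategy as offered.

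**Conclusion.** The point holds as a mismatch of populations. The 5% limit applies to post-CRT good responders, while section 8.3 creates a second group of deferring patients who can have the same event and whom section 4.2 would consider. The gap follows from the text, given the natural reading of the heading. Its size does not: the 9-41% rests on assumed good-response and conversion shares and on all good responders deferring.

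A reader might conclude that a safety signal in converters would go unseen. The documents do not support that, because the events are recorded, can be summarised and are open to the DMEC. What is supported is narrower: the one stated threshold does not count them. The matter deserves correction because it is cheap to correct and bears on the phase III decision.

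**What to change.** Reconcile sections 4.2 (objective 4), 8.3, 11.3 and 14.2.2. Move the regrowth limit out of the good-responder list and state that the existing 5% is assessed among intervention patients who start deferral of surgery, whichever MRI led to it. Name that group as the denominator. Show the proportion overall and for each entry route (post-CRT MRI, post-chemotherapy MRI), so that adding converters does not mask events in post-CRT good responders. Report the good-responder intention-to-treat proportion alongside. The 5% figure and patient care do not change.

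The cost is a wording change. Deferring patients from both routes already follow the section 11.2.1 schedule and its SURVEILLANCE Form. Patients who decline deferral follow the control-arm forms, but they add only to the denominator of the intention-to-treat figure.

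The downside is imprecision. In a route with fewer than 20 patients a single event exceeds 5% (1/19 = 5.3%). With no events, the upper two-sided 95% limit, 1 − 0.025^(1/n), is 41% for n = 7 and 14% for n = 24. Route figures should therefore be read as counts with intervals that inform judgement, in keeping with the advisory wording.
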